3.5 Randomization

Randomization is done by blocks that are of unknown size to the investigators and sponsor by drawing of sealed, opaque envelopes provided by the GCP-unit of Copenhagen University.

At the time of randomization patients are given consecutive numbers of participation. Randomization will take place after the informed consent forms have been signed and the run-in period has been completed. Numbers will be noted in the participants’ CRF and in the patients’ medical file.

### 3.6 Study Population

Potential study participants are patients with CKD stages 3-4 (50), who at the time of recruitment are attending the outpatient clinics at the Departments of Nephrology at either Herlev Hospital or Rigshospitalet. Sponsor-investigator will be recruiting at both sites and all participants will be seen only at Herlev Hospital during the study period. Contact with potential participants will be made during a normal visit to the clinic or during admission to the ward.

Patients who fulfil inclusion criteria will be offered participation in the study. There is no financial compensation made in case of participation. Study medication is given free of charge.

### 3.7 Inclusion criteria

Patients are eligible when the following requirements are met:

- 18 years ≤ age ≤ 80 years
- voluntarily signed informed consent
- 15 ml/min/1,73 m^2^ ≤ eGFR < 60 ml/min/1,73 m^2^
- BP ≥ 130/80 mmHg or undergoing anti-hypertensive treatment

### 3.8 Exclusion criteria

Patients are ineligible for participation in the study if one of the following conditions is present:

- p-potassium is > 5.0 mM
- allergy to contents
- treated with spironolactone
- treated with potent inhibitors of CYP3A4 (see SPC for details)
- treated with lithium, ciclosporin, tacrolimus, prednisolone, or other immunosuppressing drug
- inborn errors of metabolism (see SPC for details)
- pregnancy or lactation
- fertile woman, not using safe contraception devices
- dementia or other psychiatric disorder, making understanding of the study conditions impossible
- other severe, chronic illness besides CKD, including liver insufficiency, according to investigators’ judgement
- vascular surgery including stenting or graftimplantation on a. brachialis, aorta or the carotid arteries
- systolic BP > 200 mmHg
- immeasurable pulse amplitude

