### 3.2 Design

The study is a prospective, randomized, controlled, parallel group, phase IV study.

| Week number | -4 | 1 | 2 | 4 | 8 | 12 | 16 | 20 | 24 |
| --- | --- | --- | --- | --- | --- | --- | --- | --- | --- |
| Visit number |  | 1a/1b | 2 | 3 | 4 | 5a/5b | 6 | 7 | 8a/8b |

A BP target of 120-130/80-90 is set and investigators will strive to keep this constant in patients throughout their enrolled period. Therefore a run-in period of 4 weeks has been planned. All patients are to continue on their normal medication including blockers of RAS, which most of these patients receive before enrolment. If anti-hypertensive treatment needs to be intensified, this is done by adding beta blocker, calcium antagonist or methyldopa. If BP is lower than target pressure medication will be withdrawn, primarily via reduction in calcium antagonism or beta blockade, while RAS-blockade in the initial form is aimed to be kept as it was.

If study participants fail to tolerate the full dose of eplerenone 50 mg once daily, dose will be reduced to 25 mg once daily. In case of the patients receiving potassium supplements at time of enrolment these will be withdrawn before start of intervention.

Participants are randomized after the run-in period and are given consecutive numbers of identification.

The study plan is identical for the two groups.

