AMBPs are automatically measured blood pressures during ordinary daily activities for a time period of approximately 24 hours. AMBP has been found reproducible in population studies (25-30), hypertensive populations (46) and diabetics (47). The reproducibility of AASI has been proven less reliable in an essentially hypertensive population (48) . The brachial BP is measured in the office using the ABPM equipment on the non-dominant arm. After manual measurements the apparatus will automatically measure the BP every 15 minutes in daytime, which is defined from 7 am until 11 pm. Hereafter the measurements will be performed every 30 minutes from 11 pm till 7 am (49). All patients receive a diary in which they are to make notes of physical activity, meals and rest as well as bedtime and rising time in the morning. For calculation of AASI a minimum of 21 readings of BP is required. These must be spread out over the whole period with at least 7 successful readings during night time. AASI is calculated in the following manner: (1-(the slope of diastolic BP/slope of systolic BP)). It follows that the stiffer the arterial tree, the more the regression line will go towards 0 and AASI thus towards 1. Previous studies have provided references for AASI in the background population. AASI for normotensive individuals is 0.57. In younger individuals AASI is 0.53 increasing to 0.72 in the elderly (30).

*Intervention – study medication*

The study medication is eplerenone, a selective aldosterone receptor antagonist. It is an approved drug, which in this study will be used on a non-appraised indication. The Summaries of Product Characteristics (SPC) in Danish will be used as reference document for evaluation of possible side effects and will be accessible at the site of investigation when the study is initiated.

Initial recommended dose is 25 mg once daily. The dose will be increased to 50 mg eplerenone in once daily dosing after 1 week. In this study eplerenone will be added to the study participants’ usual medication. The manufacturing company Pfizer Aps has been informed of the study.

*Control*

The control group will continue their usual medical therapy.

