### 3.9 Withdrawal criteria

Withdrawal form the study can be done if one of the following events occur:

- pregnancy
- other serious illness
- cardiovascular event such as myocardial infarction or stroke
- untreatable severe hyperkalaemia
- persisting increase in p-creatinine above 30% of base line value at first control visit
- unacceptable side effects
- participant’s wish to end participation before time
- doubts about the degree of compliance

Decision about withdrawal can be made by investigators. Patients withdrawn are not replaced in the study. In case of withdrawal, the patient will resume regular controls in outpatient clinics.

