### 3.13 Practical performance of study

Patients who fulfil the inclusion criteria and who are interested in participating in the study are informed about the study. The written information is handed out and will be thoroughly explained. A form of written informed consent is to be signed by the patient and the informant/investigator. If consent is given, dates for the study days will be given.

Demographic data will be registered.

Randomization: When inclusion criteria are met including the performance of a screening for PW measurements and the run-in period has been completed, patients are randomized to the active treatment arm with eplerenone or the control arm for 24 weeks.

Planning:

A deviation of ± 1 week from the initially planned date for visits is permitted. Collection of 24 hour urine is allowed for at time deviation of ± 3 days with respect to blood sampling. Participants’ visits are planned to be identical in both groups.

Visits are planned as shown below:

| ***Visit number*** | ***Time with reference to inclusion for the individual patient*** | ***Purpose of visit*** | ***Estimated time used for the visit*** |
| --- | --- | --- | --- |
|  | Screening | signing of written informed consent, PW measurement test, ECG, blood sampling, demographic data noted | 1-1½ hours |
| 1a | Week 1 | randomization, PW measurement, AMBP, blood sampling, 24 h urine, study medication handed out | 1 hour |
| 1b | Week 1 | return of AMBP device | 10 minutes |
| 2 | Week 2 | blood sampling, BP, increase in study medication | 30 minutes |
| 3 | Week 4 | blood sampling, BP, study medication handed out | 30 minutes |
| 4 | Week 8 | blood sampling, BP, study medication handed out | 30 minutes |
| 5a | Week 12 | PW measurement, AMBP, blood sampling, 24 h urine, study medication handed out | 1 hour |
| 5b | Week 12 | return of AMBP device | 10 minutes |
| 6 | Week 16 | blood sampling, BP, study medication handed out | 30 minutes |
| 7 | Week 20 | blood sampling, BP, study medication handed out | 30 minutes |
| 8a | Week 24 | PW measurement, AMBP, blood sampling, 24 h urine, study medication and packages returned | 1-1½ hours |
| 8b | Week 24 | return of AMBP device | 10 minutes |

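### Section 3.8 excludes spironolactone but no other potassium-sparing diuretic, so eplerenone can be added to one already in use at enrolment

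*Protocol*

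**What the plan says.** Protocol 3.8 excludes patients with p-potassium above 5.0 mM and patients "treated with spironolactone". Its other drug exclusions are potent CYP3A4 inhibitors, lithium and immunosuppressants. It names no other aldosterone antagonist and no other potassium-sparing diuretic.

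On background treatment, 3.2 says: "All patients are to continue on their normal medication including blockers of RAS, which most of these patients receive before enrolment". One source of potassium is removed: "In case of the patients receiving potassium supplements at time of enrolment these will be withdrawn before start of intervention".

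On the intervention, 3.4 says "In this study eplerenone will be added to the study participants", referring to their usual medicines. Treatment starts at 25 mg, and "The dose will be increased to 50 mg eplerenone in once daily dosing after 1 week". Under 3.7, eGFR may be as low as 15 ml/min/1.73 m².

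**The concern.** The protocol plainly recognises hyperkalaemia as a hazard of this drug in this population. It caps entry potassium, stops potassium supplements, excludes spironolactone, and lists hyperkalaemia among the common side effects in the ethical considerations. Yet it stops one avoidable source of potassium and leaves another in place, without giving a reason.

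A second potassium-sparing diuretic raises the same kind of concern as spironolactone. The Background section itself gives use as a potassium-sparing diuretic among the indications for eplerenone. Giving two such drugs together, often on top of a RAS blocker and with severely reduced kidney function, is a foreseeable route to hyperkalaemia that an eligibility line could close.

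What is at stake is the safety of a small and unknown number of participants in the eplerenone arm. Eligibility belongs in the protocol, so a separate statistical analysis plan would not be expected to settle it.

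**Working it through.** No arithmetic applies. The check is to take one hypothetical patient through every rule that bears on entry, background treatment and dosing.

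**The patient.** Aged between 18 and 80, eGFR 15, on an ACE inhibitor and amiloride, p-potassium 5.0 mM, no other relevant illness or drug, consent given. Amiloride is an assumed example; the documents do not say which diuretics the clinic patients take.

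**Inclusion (3.7).**
- The age and consent criteria are met.
- The eGFR criterion is met, because 15 is the lower bound and is included.
- The blood-pressure criterion is met, because antihypertensive treatment suffices.

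**Exclusion (3.8).**
- The potassium criterion excludes values strictly above 5.0 mM, so 5.0 passes.
- The spironolactone line does not apply.
- The lines on CYP3A4 inhibitors and on lithium and immunosuppressants address other drugs.
- The line on other severe chronic illness concerns disease, is left to the investigator's judgement, and is not aimed at co-medication.

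**Background treatment (3.2).**
- Normal medication continues, so amiloride stays.
- Only potassium supplements are stopped.
- If blood pressure falls below target, the drugs reduced first are calcium antagonists and beta blockers, so that rule does not remove amiloride either.

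**Intervention (3.4).** Eplerenone is added at 25 mg and then raised to 50 mg.

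The patient is therefore eligible and, if allocated to eplerenone, takes both drugs.

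**What each safeguard does.**

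| Safeguard | Where | When it acts | Keeps the combination out? |
|---|---|---|---|
| Potassium limit of 5.0 mM | 3.8; sampling in 3.11 | Before eplerenone | No; it does not show the combined effect |
| Supplements stopped | 3.2 | Before eplerenone | No; it concerns a different source |
| Start at 25 mg | 3.4 | First week | No; it limits the initial dose |
| Repeated potassium tests | 3.11, 3.13 | On treatment | No; they detect a rise |
| Reduction to 25 mg if 50 mg is not tolerated | 3.2 | After a problem appears | No |
| Withdrawal | 3.9 and the adverse-event section | After a problem appears | No |

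The product summary does not close the gap on the protocol's own terms. Section 3.4 cites it for evaluating side effects, and 3.8 refers to it for the details of two exclusions (CYP3A4 inhibitors and inborn errors of metabolism). It is not adopted as a general eligibility rule.

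**The case against.** The strongest reply is that the gap is narrow and several safeguards surround it. Much of that is right.

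- **Only existing users are affected.** If blood-pressure treatment has to be intensified, 3.2 allows a beta blocker, calcium antagonist or methyldopa. A potassium-sparing diuretic is not among the drugs to be started for blood pressure during the trial. This stands, and it limits the point to patients already on such a drug at enrolment.
- **The entry limit already reflects the diuretic.** Potassium is measured at screening and again at visit 1a while usual medication continues, so the effect of the existing diuretic is in the value. This also stands, but the added effect of eplerenone is not in it.
- **An attentive investigator would notice.** Medication is registered under 3.10. True, but no written rule tells the investigator to exclude the patient.

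Three stronger readings are tempting, and the documents support none of them.

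- A reader might infer that nothing can be done until a patient reaches "untreatable severe hyperkalaemia". Section 3.9 also lists unacceptable side effects, the adverse-event section says such participants will be withdrawn, and 3.2 allows a lower dose. Action can come earlier.
- A reader might take the visit table (visit 2 is described as "blood sampling, BP, increase in study medication") and the one-week visit tolerance as a measure of the harm. The schedule is the same whether or not a patient takes a diuretic, so the spacing says nothing about this particular gap. Nor does the protocol say that the dose is raised before the potassium result is known.
- A reader might infer that current eplerenone users, whom 3.8 does not bar either, could dilute the PWV contrast materially. Their number is not given and is probably near zero, and some might be excluded for other severe illness. The stated clinical experience of the group with eplerenone does not show that clinic patients are taking it now. This is a minor wording point.

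**Conclusion.** The point holds in a limited form. For a patient already on a potassium-sparing diuretic other than spironolactone, no rule in the protocol prevents eplerenone from being added, at eGFR down to 15 and usually with a RAS blocker. The existing safeguards lower the risk, but they either precede the combined exposure or respond to its effect.

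The size cannot be stated. The documents give neither the frequency of such diuretic use nor the added risk of hyperkalaemia, so no rate is claimed. The practical importance rests on the assumption that at least some patients in the recruiting clinics take such a drug. If none do, the gap is one of wording only.

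This is a cheap improvement for patient safety. It does not call the sample size or the primary comparison into question.

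**What to change.** In 3.8, replace the spironolactone line with: *treated with any aldosterone receptor antagonist (spironolactone or eplerenone) or other potassium-sparing diuretic*. This also settles the minor point about current eplerenone users.

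Add that a patient whose clinic has already switched such a drug for its own reasons may be screened once blood pressure is stable, before the 4-week run-in begins. Stopping the diuretic during run-in is less attractive. The run-in exists to hold blood pressure steady, and the Background section names blood pressure as an independent influence on PWV, the primary endpoint.

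The cost is one line of text and a few more exclusions. Their number is not given, and it has to be weighed against an expected recruitment of one patient per week.

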### 3.9 Withdrawal criteria

Withdrawal form the study can be done if one of the following events occur:

- pregnancy
- other serious illness
- cardiovascular event such as myocardial infarction or stroke
- untreatable severe hyperkalaemia
- persisting increase in p-creatinine above 30% of base line value at first control visit
- unacceptable side effects
- participant’s wish to end participation before time
- doubts about the degree of compliance

Decision about withdrawal can be made by investigators. Patients withdrawn are not replaced in the study. In case of withdrawal, the patient will resume regular controls in outpatient clinics.

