## Statistics

Power calculations have been made based on a minimal clinically relevant difference on the primary end point PWV of 1 m/s. It has been shown that an increase of PWV of this size increases mortality by 39%(19).

From our own data we have a standard deviation of 1.5 on PWV. At a level of significance of 0.05 and power 0.8 a calculation of number of participants for each group should reach 37. We plan to include 40 patients in each group.

Two-sample t test power calculation

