**n = 36.3058**

delta = 1

sd = 1.5

sig.level = 0.05

power = 0.8

alternative = two.sided

NOTE: n is number in *each* group

Patients who are with drawn are not replaced.

Differences in PWV will be statistically examined using paired t tests.

The secondary effect parameters will also be examined using this statistic method. For the groups as a whole two sample t test will be applied. If data do not fit the normal distribution they will be transformed.

1. ***Quality control***

Normal procedures for quality control will be followed, see ICH GCP Guidelines. Data will be monitored by The GCP unit at Copenhagen University Hospital, Bispebjerg Hospital, [name], [name], [name]. As informed consent is given, a permission from the participant for the Danish Medicines Agency and the GCP unit to have access to the patient’s hospital medical files will be sought. A copy of the text is available (in Danish).

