## Adverse events and side effects

Registration and reporting of side effects follow the given laws. In the following the document of referral is in Danish: *Bekendtgørelsen for kliniske forsøg med lægemidler på mennesker* (The notice for clinical studies using pharmaceutical drugs on humans). Suspected and unexpected adverse reactions (SUSAR), that are either lethal or life threatening will be reported to the Danish Medicines Agency within 7 days of notice to the sponsor-investigator and at the latest at day 8 after this the Agency will be informed of all actions taken on the follow up. All unexpected and serious suspected side effects will be reported to the Danish Medicines Agency at the latest 15 days after it has come to the attention of the sponsor-investigator. Serious adverse reactions (SAR) will be reported on a yearly basis to the Regional Ethics Committee. Events will be recorded on the patients’ CRF excepting laboratory results that lie outside the reference values but where no action is taken to either change the study medication or institute treatment. Common viral diseases such as colds or flus will not be reported. Finally uncomplicated urinary tract infections will not be reported.

Events and side effects will be reported in the final report to the Danish Medicines Agency after termination of the study. Events and side effects will be registered from the time of initial dosing of study medication until withdrawal.

In case of unacceptable side effects the participant will be withdrawn from the study. The patient will continue in the out patients clinic of nephrology as long as this is required.

The study can be terminated before time according to the sponsor-investigator’s judgement.

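### Withdrawal is defined as leaving the study rather than stopping the drug, so week-24 PWV, creatinine and eGFR may be lost mainly from the eplerenone arm

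*Protocol*

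**What the plan says.** Section 3.9 of the protocol (Withdrawal criteria) sets out when a patient may be withdrawn from the study. Beside pregnancy, other serious illness, a cardiovascular event and the patient's own wish, the list has severe hyperkalaemia that cannot be treated, unacceptable side effects, "persisting increase in p-creatinine above 30% of base line value at first control visit" and "doubts about the degree of compliance". The wording is permissive: withdrawal can be done, and investigators can decide it. What follows is stated in one sentence: "In case of withdrawal, the patient will resume regular controls in outpatient clinics".

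The section Adverse events and side effects is stricter on one of these reasons: "In case of unacceptable side effects the participant will be withdrawn from the study". It also ends the registration of events at withdrawal.

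The Statistics section says "Patients who are with drawn are not replaced". It plans 40 patients per group.

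PWV is measured at visits 1a, 5a (week 12) and 8a (week 24), according to the visit table in section 3.13. Neither that table nor any other section describes a PWV measurement at or after withdrawal. Under section 3.4 the control group stays on its usual therapy, and no placebo is given. Section 3.3 makes PWV the primary endpoint and lists eGFR and p-creatinine among the secondary ones.

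**The concern.** The plan treats two different events as one: a patient stops taking eplerenone, and a patient stops being measured. PWV is a tonometry measurement made by the trial's own observer under standard conditions. The protocol does not provide for it in routine outpatient care, so a withdrawn patient's week-24 value is simply absent. An analysis plan can choose an analysis set or an imputation model, but it cannot recover a measurement that was never taken.

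The loss is unlikely to be even between the arms. Unacceptable side effects of study medication and doubts about tablet-taking can hardly arise in patients who receive no study tablets. The Ethical considerations section lists reduced kidney function and hyperkalaemia among the common effects of the drug, and both correspond to withdrawal triggers. The decision lies with investigators, and no placebo conceals the arm.

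If patients who leave eplerenone differ in PWV course from those who stay, the week-24 comparison of observed values no longer compares the groups that were randomised. For creatinine and eGFR the link is more direct, because a large creatinine rise is itself a reason to withdraw.

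**Working it through.** **1. Reproduce the plan's own figure.** Inputs from the Statistics section: "Power calculations have been made based on a minimal clinically relevant difference on the primary end point PWV of 1 m/s", SD 1.5, and "At a level of significance of 0.05 and power 0.8 a calculation of number of participants for each group should reach 37", with "alternative = two.sided". For a two-sample t test the noncentrality is delta / [SD × √(1/n1 + 1/n2)] on n1 + n2 − 2 degrees of freedom. Solving for power 0.80 with equal arms gives n = 36.3 per group, rounded up to 37. This agrees with the protocol's 36.3058. The sample-size figure is correct.

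**2. Margin for losses.** 1 − 37/40 = 7.5% per arm. No withdrawal rate is stated anywhere.

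**3. Power when the loss is on eplerenone only.** Delta 1, SD 1.5, two-sided 0.05, all 40 controls measured:

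| Eplerenone / control | Assumed loss on eplerenone | SE = 1.5 × √(1/n1 + 1/n2) | Power |
|---|---|---|---|
| 40 / 40 | 0% | 0.335 | 0.84 |
| 36 / 40 | 10% | 0.345 | 0.82 |
| 34 / 40 | 15% | 0.350 | 0.805 |
| 32 / 40 | 20% | 0.356 | 0.79 |

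Power falls to 0.75 at 20% loss only if both arms lose that share (32 / 32).

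**4. Possible bias.** Assume that the fraction f of eplerenone patients with the highest withdrawal propensity is lost, that propensity and PWV change are jointly normal with correlation r, and that no controls are lost. The mean of the retained patients then shifts by

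bias = r × SD × φ(z) / (1 − f), where z is the (1 − f) quantile of the standard normal distribution and φ its density.

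- f = 0.10: z = 1.2816, φ(z) = 0.1755, and 0.1755 / 0.90 = 0.195.
- f = 0.20: z = 0.8416, φ(z) = 0.2800, and 0.2800 / 0.80 = 0.350.

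With SD = 1.5:

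| r | 10% lost | 20% lost |
|---|---|---|
| 0 | 0 | 0 |
| 0.1 | 0.03 m/s | 0.05 m/s |
| 0.3 | 0.09 m/s | 0.16 m/s |
| 0.5 | 0.15 m/s | 0.26 m/s |

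For example, 0.5 × 1.5 × 0.350 = 0.26.

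**5. What that does to the test.** Put the bias in place of delta in the power formula of step 1. With no true effect, the two-sided rejection rate at 36 versus 40 goes from 5.0% (r = 0) to 5.1% (r = 0.1) and 7.0% (r = 0.5). At 32 versus 40 it goes from 5.0% to 5.2% and 11.3%.

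The values of f and r are assumptions; the documents give neither. The SD of 1.5 is the protocol's SD of PWV, used here for PWV change because no SD of change is given.

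**The case against.** Several points limit the concern.

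- **Section 3.9 permits withdrawal and does not require it.** A reader might infer that every creatinine rise above 30% is censored by rule. The text does not support this: the rise must persist, the criterion is tied to the first control visit, and the investigator may decide otherwise. The values up to withdrawal are recorded. Only the side-effect wording in the adverse-events section is mandatory.
- **The criteria cover both arms.** Serious illness, cardiovascular events, pregnancy or a patient's wish can remove controls, and section 3.4 speaks of compliance with participation as well as with medication. A reader might infer that the loss is confined to eplerenone; the documents support only that it would be mainly there.
- **The protocol limits the losses.** Section 3.2 provides a dose reduction for intolerance. Section 3.8 excludes patients with potassium above 5.0 mM. Only severe hyperkalaemia that cannot be treated is a trigger. PWV is also measured at week 12, so a patient who leaves later still has one value after baseline.
- **The documents give no figure for the bias.** There is no withdrawal rate, no correlation and no established sign.
- **No completer analysis is specified.** The analysis set and missing-data handling may be in an analysis plan that was not available.

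All of this stands, and it lowers the weight of the point. It does not remove the core: the protocol provides no PWV after withdrawal, and no later document can supply one.

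**Conclusion.** The design weakness is real and fixed in the protocol. Leaving treatment and leaving measurement are merged, the main treatment-related triggers belong to one arm, and the week-24 value of the primary endpoint is lost when they apply.

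The size is unknown. Under the assumptions in the working, the bias is about 0.03-0.26 m/s, or 3-26% of the 1 m/s target, and zero if withdrawal is unrelated to PWV change. The sign is not established: a bias in favour of eplerenone is plausible if patients who tolerate the drug badly also do worse on PWV, but nothing in the protocol shows that they do.

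A reader might also infer that the trial becomes underpowered once more than three patients per arm are lost. That does not follow from one-sided loss: with controls complete, six losses on eplerenone still leave power at 0.805, and eight leave 0.79. Power is a minor point; possible bias and the lost renal and safety follow-up matter more. This should be fixed, but it does not by itself invalidate the trial.

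**What to change.** Leave the clinical reasons for stopping study medication as they are, and make three changes by a short amendment.

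1. Reconcile the permissive wording of section 3.9 with the mandatory wording on unacceptable side effects in the adverse-events section.
2. Define stopping study medication and leaving the study as separate events. Unless the patient withdraws consent or cannot attend, those who stop medication keep the scheduled week-12 and week-24 visits (5a and 8a) with PWV, ambulatory blood pressure and laboratory tests.
3. State that patients are analysed in the arm to which they were randomised, whether or not they are still on treatment.

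The cost is one or two visits already in the schedule for the few patients who stop early. The downside is that off-drug follow-up dilutes the on-drug effect to some extent; an on-treatment sensitivity analysis can show that effect. The change has to be in place before patients withdraw, since missed measurements cannot be made up.
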